## 5. Background

The use of high-dose chemotherapy (HDC) and autologous stem cell transplantation (SCT) has improved the outcome of hematologic malignancies such as multiple myeloma (MM) and (non-) Hodgkin's lymphoma (NHL/HL). It has become standard of care in these diseases in first line and at relapse respectively. However, the long term side effects of this treatment can have a strong negative impact on quality of life [1]. Up to 75% of patients interviewed at least twelve months post-SCT report severe and persistent fatigue, and are compromised in their ability to engage in normal physical activities [2] About 30% is not able to return to work during the course of the first two years after treatment [3]. Physical deconditioning, resulting from diminished cardiovascular and pulmonary function, reduced muscular strength and cachexia were also highly prevalent [4]. With increasing survival rates, attention should not only be focused on improving cure rates but also on improving recovery after treatment, thereby increasing long-term quality of life. Preliminary results show that exercise interventions can counter the physical deconditioning after SCT, and thus might also improve the quality of life in these patients.

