#### 6. Return to work

The following indicators of return to work will be measured: (1). Time to partial and to full RTW (meaning number of calendar days between end of treatment and first day at work), (2) time to full RTW corrected for partial RTW, (3) partial and full RTW rate at T=1 and T=2. (4) Details on hours worked per week, nature of work, and return to a different job will also be recorded.

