## 11. Statistical considerations

### 11.1 Sample size and statistical power calculations

The sample size calculations were estimated for the primary outcomes for a two-sided  $\alpha=0.05$ , and a power of 80%. We expect a between group difference of  $7.5\pm 7$  ml/kg/min in VO2 max, of  $0.2\pm 0.1$  kg in hand grip strength and of  $3.5\pm 4$  in fatigue (MFI). We need between 25 and 42 subjects per group to detect these differences between the intervention and control group. Assuming a dropout rate of 30% (15% of the patients in our database who had undergone autologous SCT for MM< HL or NHL have an early relapse within 6 months, and are therefore expected not to complete the intervention program, and may in addition not be able to complete the study assessments. Furthermore, 15% may drop out because of other reasons) we need to enrol 60 subjects per group.

In the five participating transplant centers, yearly 180-210 autologous SCT are being performed. In 2007 170 patients received an autologous SCT for MM, HL or NHL (MM: 105 patients; NHL: 55 patients, HL: 10 patients). Taking in consideration all patients who will be ineligible for randomization (treatment related mortality SCT 4.3% = 3 patients; 10% of MM patients receiving an allogeneic SCT = 11 patients; 20% of MM patients having extensive osteolytic lesions with risk of fracture = 22 patients) we estimate that of the 170 patients transplanted yearly, 137 will be eligible, the majority of whom are expected to be interested in participating in the study (60 patients are needed on a yearly basis). This indicates that the proposed study is feasible with a projected inclusion time of 2 years.

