#### 11.2.2 Primary analysis

Data will be analyzed on an intention-to-treat basis: patients who have been randomized to the intervention group but for whatever reason do not start or continue with training, will be encouraged to still undergo the assessments. Additionally, a per-protocol analysis will be performed with the patients who have completed at least 75% of the training sessions. Longitudinal regression analysis will be used to assess changes in each outcome measure. The two follow-up measurements will be defined as dependent variable and multi-level analysis with three levels will be used, 1) treatment center 2) time of follow-up measurement (values corresponding with performance at  $t=1$  and  $t=2$ ); 3) individual.

Regression coefficients indicate differences between intervention and control group. Regression models will be adjusted for baseline values, age and gender. To test our hypothesis that the changes in physical fitness will mediate, in part, the beneficial effect of exercise on fatigue and quality of life, a mediation analysis will be performed using Latent variable structural equation modelling.

For *hypothesis 3* scores on the self-reported measures of mood state, physical activity and HRQL will be calculated according to existing scoring algorithms. Next multilevel longitudinal regression analyses will be conducted to assess differences in each outcome measure between intervention and control group at follow-up. Regression coefficients indicate differences between intervention and control groups.

Regression models will be adjusted for gender, age and baseline values. For *hypothesis 4* (examining the differences in return to work), we will use Kaplan Meier's and the Cox proportional hazard regression for recurrent events. The general idea behind this analysis is that the different time periods are analysed separately adjusted for the fact that the time periods within one patient are dependent. Recurrences of sick leave for any reason during follow-up will be added to the Cox proportional hazards model with the

time to event approach, in which only the transitions from sick leave to return to work are taken into account.

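### Kaplan-Meier is named for time to return to work although death and permanent work exit preclude it; a percentage read from the curve would be too high, probably by a few points

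*Protocol*

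**What the plan says.** Hypothesis 4 (Protocol Section 5.5) is a higher partial and full return-to-work rate than with standard care alone. Section 9.2, item 6, defines time to return as the "number of calendar days between end of treatment and first day at work" and lists, as a separate indicator, "partial and full RTW rate at T=1 and T=2".

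For the analysis, Section 11.2.2 says "we will use Kaplan Meier's and the Cox proportional hazard regression for recurrent events". Repeat sick leave is added to the Cox model in such a way that "only the transitions from sick leave to return to work are taken into account". No role is given to death, retirement, full disability or relapse.

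Section 11.1 states that 15% of comparable patients "have an early relapse within 6 months" and that they "are therefore expected not to complete the intervention program, and may in addition not be able to complete the study assessments". It adds: "Furthermore, 15% may drop out because of other reasons". The only return-to-work level in the protocol is a literature figure in Section 5: "About 30% is not able to return to work during the course of the first two years after treatment".

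**The concern.** Kaplan-Meier knows two states, event and censored. If only transitions to work are events, a patient who dies or leaves the workforce for good is censored. The estimator then treats that patient as someone who would have gone on to return at the same rate as those still observed. For the dead this is false by definition, and for permanent exit it is false by construction.

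The consequence falls on the absolute percentages. One minus Kaplan-Meier no longer estimates the share of patients who return to work, although a return-to-work rate is what hypothesis 4 is about. The bias is upward in both arms.

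**Working it through.** The protocol states no return-to-work percentage, event count or power for this outcome, so there is no figure of its own to reproduce. The size is therefore illustrated under constant hazards.

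**Inputs**
- Return to work: Section 5 has 30% not back at two years, so *r* = −ln(0.30)/24 = 0.0502 per month. This is an illustration, not a planning value. The source listed for it is, by its title, a study of allogeneic transplantation.
- Death: no rate is given. Assumed 5% or 10% per year, so *c* = −ln(0.95)/12 = 0.0043 or −ln(0.90)/12 = 0.0088 per month.
- Relapse: Section 11.1 has 15% within 6 months, so *c* = −ln(0.85)/6 = 0.0271 per month. Nothing is given beyond month 6.
- Horizon: the text does not settle whether T2 is 12 months after T0 or after T1. With an 18-week program (about 4 months), T2 is at 12 or about 16 months. The clock is started at T0 for simplicity.

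**Formulas**
- One minus Kaplan-Meier: 1 − exp(−*rT*)
- Cumulative incidence: *r*/(*r*+*c*) × [1 − exp(−(*r*+*c*)*T*)]

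Example, death at 10% per year, 12 months: 1 − exp(−0.0502 × 12) = 45.2%, against 0.0502/0.0589 × [1 − exp(−0.0589 × 12)] = 0.851 × 0.507 = 43.2%. The gap is 2.1 points before rounding.

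| Events that end the record | 12 months: 1−KM / cumulative incidence / gap | 16 months: 1−KM / cumulative incidence / gap |
|---|---|---|
| Death, 5% per year | 45.2 / 44.2 / 1.0 | 55.2 / 53.6 / 1.6 |
| Death, 10% per year | 45.2 / 43.2 / 2.1 | 55.2 / 52.0 / 3.2 |
| Every relapse, first 6 months only, no later return | 45.2 / 40.4 / 4.8 | 55.2 / 48.9 / 6.3 |
| Every relapse, 15% per 6 months to T2, no later return | 45.2 / 39.2 / 6.0 | 55.2 / 46.1 / 9.1 |

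The last row is the worst case for how relapse is treated. It softens quickly:
- If half as many relapses act this way (7.5% per 6 months), the gap is 3.0 points at 12 months and 4.7 at 16.
- If relapsed patients still return at half the hazard, it is 2.7 and 3.9 points.
- If they return at an unchanged hazard, it is 0.
- At T1 (about 4 months) even the worst case gives 1.0 point.

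The assumed return level matters too. With 30% to 80% back by 12 months on the Kaplan-Meier scale, the worst-case gap runs from 4.1 to 8.8 points at 12 months and from 6.6 to 11.4 at 16.

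**Arm contrast.** Assume a return-to-work hazard ratio of 1.5 and equal relapse in both arms, worst case:
- 12 months: Kaplan-Meier 59.5 − 45.2 = 14.2 points (unrounded inputs); cumulative incidence 52.0 − 39.2 = 12.8. Change about 1.5.
- 16 months: 70.0 − 55.2 = 14.8; 59.2 − 46.1 = 13.2 (unrounded inputs). Change about 1.7.

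By Greenwood's formula with 60 per arm, Var = *S*² × *r*/(*r*+*c*) × [exp((*r*+*c*)*T*) − 1]/60. The standard error of the 12-month difference is then about 9.9 points, so the change is about 0.15 standard errors.

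**The case against.** A reader might infer that the T2 return-to-work percentages are overstated by 6 to 9 points at the plan's own relapse rate. The protocol does not support that, for four reasons.

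- Section 9.2 lists the T1 and T2 rates apart from time to return, and nothing ties them to the Kaplan-Meier curve. A simple proportion of all patients would not carry this bias. This stands, with one reservation: a proportion among only those without relapse who still respond would share it. Under the constant hazards above, that proportion equals one minus Kaplan-Meier.
- Relapse is not a censoring event in this protocol. Section 8.3 makes early relapse a reason to stop protocol treatment. Section 9.4 asks patients who stop treatment to stay in follow-up, and Section 11.2.2 applies intention to treat. Section 11.1 says only that relapsed patients may miss assessments. This stands.
- The 15% covers 6 months, and carrying it to T2 is an extrapolation. Relapse is also an exclusion criterion (Section 7.3), so relapses before entry never reach the trial. This stands.
- Hypothesis 4 is comparative, and the comparison hardly moves. This stands.

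It can also be said that censoring rules belong in a statistical analysis plan that is not shown. That covers detail, but the protocol itself names the estimator and the only transition that counts. For death and permanent work exit, any censoring rule within Kaplan-Meier leads to the same bias.

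**Conclusion.** The point holds in a limited and conditional form. Section 11.2.2 names an estimator that cannot give the proportion returning to work when death or permanent work exit occurs. Any percentage read from that curve would be too high. With death alone, at the assumed 5 to 10% per year and the Section 5 return level, the excess is about 1 to 3 points at 12 to 16 months. Permanent work exit would add to this by an amount the protocol gives no means to estimate. The figure of 6 to 9 points is a worst case resting on the relapse assumptions set out above, not a consequence of the plan as written. The between-arm difference changes by roughly 1.5 points in that worst case, and the Cox hazard ratio remains usable as a cause-specific quantity. The outcome is secondary, so this affects how return-to-work percentages are reported and not the trial's main conclusions.

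**What to change.** In Section 11.2.2:

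- Replace Kaplan-Meier for time to partial and to full return to work by the Aalen-Johansen cumulative incidence, with death and permanent exit from work (retirement, full disability) as competing events.
- Do not censor at relapse. Keep relapsed patients at risk, as not returned, for as long as they are followed.
- Add a sensitivity analysis that counts relapsed patients lost to follow-up as not returned. Turning relapse into a competing event only once questionnaires stop would let missing data define the event, so that route should be avoided.
- Keep the Cox model and label its hazard ratio cause-specific.

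The cost is small. The text change is short and the software is standard. Relapse is already retrieved from medical records (Section 9.3). The return-to-work questionnaire must also record dates of retirement or full disability, which Section 9.2 does not list. Reported return-to-work percentages will come out slightly lower.

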### 11.2.3 Economic evaluation

This project will include an economic evaluation in collaboration with an expert in this field from the EMGO+ Institute for Health and Care Research. The aim of the economic evaluation will be to determine and compare the difference in total societal costs between the intervention and the control group and to relate these costs to the difference in effects between the two groups for the primary outcomes. The economic evaluation will be performed according to the intention-to-treat principle and from a societal perspective.

Both cost-effectiveness and cost-utility analyses will be performed. The cost-effectiveness ratios will be calculated by dividing the difference between the mean costs of the two treatment groups by the difference in the mean effects of the two treatment groups. This ratio will include the primary clinical effect measures of the trial. The cost-utility ratio will express the additional costs of the intervention per quality adjusted life year (QALY). Utilities will be measured using the EuroQol (EQ5D) at baseline, at the end of the treatment and at twelve months. The EuroQol is a health-related quality of life instrument that provides a single index of an individual's quality of life. It consists of 5 dimensions resulting in 243 possible health states [52]. The health states will be valued using Dutch tariffs.

Multiple Imputation (MI) using the Multivariate Imputation by Chained Equations (MICE) will be used to impute missing cost and effect data. Bootstrapping will be used to estimate confidence intervals around the mean differences in costs between the treatment groups. The uncertainty surrounding the cost-effectiveness and cost-utilities ratios will also be estimated using bootstrapping techniques. The bootstrapped cost-effect pairs will be used to estimate cost-effectiveness and cost-utility planes, and cost-effectiveness acceptability curves. Sensitivity analysis on the most important cost drivers will be performed in order to assess the robustness of the results.

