### 7.2 Randomized controlled trial

This multicenter, prospective, single blind, RCT will compare an exercise intervention and standard care with standard care only. The 120 patients participating in the study will be randomized to either the intervention arm (n = 60) or the control arm (n = 60). In addition to the standard care, patients in the intervention arm will take part in an 18-week individualized supervised high-intensity exercise program. This program will start 6-14 weeks after SCT. Patients in the control group are treated according to standard care.

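### The economic evaluation names no baseline adjustment for its effect and QALY differences, although the clinical analysis adjusts the same primary outcomes, so precision available from data already collected is given up

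*Protocol*

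**What the plan says.** Section 11.2.3 of the protocol defines the cost-effectiveness ratio as the result of "dividing the difference between the mean costs of the two treatment groups by the difference in the mean effects of the two treatment groups". The effects meant are the primary outcomes: "This ratio will include the primary clinical effect measures of the trial". A separate sentence introduces the cost-utility ratio, as additional cost per QALY, without saying how the QALY difference is estimated. On the utilities it says "Utilities will be measured using the EuroQol (EQ5D) at baseline, at the end of the treatment and at twelve months".

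For uncertainty it says "Bootstrapping will be used to estimate confidence intervals around the mean differences in costs between the treatment groups", and it extends bootstrapping to the ratios, planes and acceptability curves. Chained-equation imputation is used to "impute missing cost and effect data". No covariate is named anywhere in 11.2.3.

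Section 11.2.2 analyses the primary outcomes by multilevel longitudinal regression and says "Regression models will be adjusted for baseline values, age and gender". The same adjustment is repeated there for mood, physical activity and quality of life.

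**The concern.** The protocol describes two estimates of the treatment effect on the same primary outcomes. One is adjusted for baseline, age and gender. The other, used in the ratio, is described only as a difference in means. The two can give different answers, and the second is the less precise when baseline predicts follow-up.

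The QALY is more exposed. Under the usual area-under-the-curve calculation, baseline utility is itself a component of the QALY and is also correlated with the later utilities. With 60 patients per arm or fewer, a chance difference at T0 would move the QALY difference, and with it the cost-utility plane and the acceptability curve, for a reason unrelated to treatment. Cost-effectiveness is the only secondary objective in section 6.

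**Working it through.** The protocol gives no correlation, EQ-5D SD or QALY difference, so there is no figure of its own to reproduce. What follows is a range under stated assumptions.

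**Inputs from the protocol.** EQ-5D at T0, T1 and T2 (11.2.3); an 18-week programme and 60 patients per arm (7.2); 42 per group as the upper end of the number needed (11.1).

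**Assumptions.** QALY as a trapezoid area; T1 at 18 weeks and T2 at 52 weeks from T0; equal SDs and one common correlation r between visits; utility SD 0.25 for the absolute figures.

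**Weights.** With T1 at 18/52 = 0.346 year and T2 at 1 year:
- T0: 0.346/2 = 0.173
- T1: 1/2 = 0.500
- T2: (1 − 0.346)/2 = 0.327

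**Formulas.**
- Slope of QALY on baseline utility: b = 0.173 + 0.827r
- QALY variance in units of the utility variance: v = 0.387 + 0.613r, where 0.387 is the sum of the squared weights
- Share of QALY variance removed by adjustment: R² = b²/v
- Ratio of adjusted to unadjusted standard error: √(1 − R²)

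| r | b | v | R² | SE ratio | SE reduction |
|---|---|---|---|---|---|
| 0.3 | 0.421 | 0.571 | 0.31 | 0.83 | 17% |
| 0.5 | 0.587 | 0.693 | 0.50 | 0.71 | 29% |
| 0.7 | 0.752 | 0.816 | 0.69 | 0.55 | 45% |

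If T2 is instead 12 months after T1, R² is 0.26, 0.45 and 0.66, and the SE ratios are 0.86, 0.74 and 0.58.

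**Effect of a chance imbalance (r = 0.5, SD 0.25).**
- SE of the baseline difference at 60 per arm: 0.25 × √(2/60) = 0.046.
- An imbalance of one SE shifts the QALY difference by 0.587 × 0.046 = 0.027.
- Unadjusted SE of the QALY difference: 0.25 × √(0.693 × 2/60) = 0.038. The shift is about 0.7 of that SE.
- At 42 per arm the shift is 0.587 × 0.25 × √(2/42) = 0.032.

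With SD 0.2 to 0.3, 42 to 60 per arm and r from 0.3 to 0.7, the shift runs from 0.015 to 0.049 QALY.

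**Clinical effect measures.** For one follow-up value adjusted for its baseline, the share of variance removed is r²: 9%, 25% and 49% at r = 0.3, 0.5 and 0.7. The SE ratios √(1 − r²) are 0.95, 0.87 and 0.71. The gain is smaller than for QALYs because baseline is not a component of the outcome.

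**The case against.** **The text does not say the means are raw.** A reader might infer that the protocol prescribes unadjusted means. It does not use that word, and a ratio of mean differences is the ordinary definition of such a ratio, compatible with adjusted means. Covariates for an economic analysis may also be in an analysis plan that is not shown. This stands as a limit on the claim. It does not remove the point: 11.2.3 gives the formula, the imputation, the bootstrap and the sensitivity analysis, all without adjustment, while 11.2.2 states adjustment twice. Imputing with baseline data does not adjust the contrast for it.

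**The formula concerns the clinical effects.** This is correct. That the QALY difference takes the same form is implied by the parallel presentation and the shared bootstrap. No QALY estimator or area rule is written down.

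**Randomisation already protects the comparison.** A reader might infer that the QALY result is biased, or that an imbalance is counted in full as treatment effect. Neither follows. The unadjusted contrast is unbiased over repeated randomisation, chance imbalance is sampling error that the bootstrap interval covers, and only the fraction b of an imbalance carries over. What remains is avoidable width, and an estimate that is off given the imbalance that happens to occur.

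**Costs are not quantified.** This also stands. The cost questionnaires start at T0 and no earlier cost measure is described, so the gain is shown for the effect axis only.

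**Conclusion.** The point holds as an inexpensive improvement to a secondary objective. Section 11.2.3 names no baseline adjustment where 11.2.2 has one for the same outcomes, so the effect estimate in the ratio is less precise than the trial's own and may disagree with it. If QALYs are an area under the EQ-5D curve and their difference is likewise unadjusted, adjustment would remove about 31% to 69% of the QALY variance for r between 0.3 and 0.7.

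A reader might infer a loss of about half as a general figure. That holds for the QALY only at r near 0.5, and for a single follow-up measure only at r near 0.7. The protocol supports no one value. All the magnitudes rest on the assumed visit times, equal SDs and common correlation, and the absolute QALY shifts also on the assumed SD. The result would remain valid without the change, but less precise than the collected data allow.

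**What to change.** State in 11.2.3 that incremental effects and incremental QALYs are estimated by regression on arm, the baseline value of the effect measure (baseline EQ-5D utility for QALYs), age and gender, within each imputed and bootstrapped data set. Estimate incremental costs alongside in the same resamples, so that the correlation between cost and effect is kept. Form the ratios, planes and acceptability curves from these adjusted differences. The same sentence can say how QALYs are calculated from the three EQ-5D measurements.

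Joint (seemingly unrelated) regression of cost and effect, and adding diagnosis as a covariate, are optional. The cost is a sentence or two in the protocol and slightly more programming. The T0 measurements are already scheduled, so no extra visit, questionnaire or patient is needed.
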